### 5.3.7 STORAGE

The vaccines will be stored according to the SOM and Local Working Instructions that will be reviewed at site initiation. They will be stored in a secure, limited access storage area under the specified storage requirements:

- DNA-HIV-PT123 must be stored at -20°C ±5°C.

- ▶ MVA-CMDR: must be stored at  $-80^{\circ}\text{C} \pm 10^{\circ}\text{C}$
- ▶ CN54gp140: must be stored at  $2-8^{\circ}\text{C}$ .
- ▶ MPLA-L: must be stored at  $2-8^{\circ}\text{C}$

#### **5.3.8 DISPENSING**

See [section 5.2.6](#).

#### **5.3.9 DOSE MODIFICATIONS & INTERRUPTIONS**

See [section 5.2.7](#).

### **5.4 GROUP C**

#### **5.4.1 NORMAL SALINE PLACEBO**

Sodium Chloride (NaCl) for injection, 0.9% will be used to draw up the placebo for each vaccine product. The volume will be matched to the vaccine at 1ml for DNA-HIV-PT123, MVA-CMDR and AIDSVAX® B/E, but 0.45ml for CN54gp140 in MPLA-L.

#### **5.4.2 TREATMENT SCHEDULE**

The target is a minimum of 556 individuals who complete the schedule, and so participants who drop out before the third injection timepoint will be replaced by randomising another eligible volunteer. Therefore up to 620 individuals could be randomised to receive placebo. As the volume of the CN54gp140 in MPLA-L is only 0.45ml and this differs from the other active vaccine volumes of 1ml, pharmacists will cover the syringe with the label so that although the individual administering the injection can determine the volume by size of syringe or weight they cannot tell if it is active or placebo.

Participants randomised to Schedule C will receive two placebo vaccines as described in [Table 6](#) at Visits 2, 4, 8 and 12.

#### **5.4.3 DOSE & ADMINISTRATION**

The volume of normal saline drawn up will match the vaccine. The 556 participants in Group C will be randomly divided in a 1:1 ratio to receive 1ml in each arm at the four timepoints or 1ml in the left arm and 0.45ml in the right arm at the four timepoints.

In the event that study staff administer the product into the opposite muscle to the one intended a deviation should be noted (see SOM for details) and revert to the correct arm for any remaining vaccinations.

#### **5.4.4 STORAGE**

Normal saline will be stored according to the SOM and Local Working Instructions in a secure, limited access storage area under the specified storage requirements:

- ▶ Placebo (NaCl): ambient temperature ( $15-25^{\circ}\text{C}$ )

#### **5.4.5 DISPENSING**

See [section 5.2.6](#).

#### **5.4.6 DOSE MODIFICATIONS & INTERRUPTIONS**

See [section 5.2.7](#).

## 5.5 PREP DRUGS

### 5.5.1 TDF/FTC

The drug to be used as PrEP control is TDF/FTC, which is approved for the treatment of HIV infection in all participating countries and for PrEP in a smaller number. Each tablet contains 245mg of tenofovir disoproxil (TDF) and 200mg of emtricitabine (FTC), both of which are nucleot/side analogue HIV-1 reverse transcriptase inhibitors. The drug will be manufactured and supplied by Gilead Sciences, Inc from clinical trial supply. It will be labelled for clinical trial use.

### 5.5.2 TAF/FTC

The drug to be used as experimental PrEP is TAF/FTC, which is approved for the treatment of HIV in Tanzania and Uganda. Each tablet contains 25mg of tenofovir alafenamide (TAF) and 200mg of emtricitabine (FTC), both of which are nucleot/side analogue HIV-1 reverse transcriptase inhibitors. The drug will be manufactured and supplied by Gilead Sciences, Inc from clinical trial supply. It will be labelled for clinical trial use.

### 5.5.3 DOSE & ADMINISTRATION

The dose is one tablet daily and administration is oral.

### 5.5.4 STORAGE

The product should be stored in the original packaging at ambient temperature and protected from moisture.

### 5.5.5 DISPENSING AND RETURNS

The PI will ensure that the tablets are dispensed in accordance with the protocol, the study specific SOM and Local Pharmacy Working Instructions as appropriate. Local Working Instructions will be reviewed at site initiation.

PrEP will be dispensed at visits 2, 4 and 7 and interim visits if required to maintain the supply through to 2 weeks after the third immunisation. Participants will be provided with 60 and 90 tablets respectively at visits 2 and 4 as they may not be able to attend the next dispensing visits for reasons outside their control. At visit 7 there will be a reconciliation of tablets and sufficient to last until visit 9 provided (see [Table 6](#)).

If visit 8 takes place later than 24 weeks from enrolment, participants may require an additional 14 days of PrEP to be dispensed at this visit to cover the period to peak immunogenicity.

A PrEP Accountability Log will be kept to record the identification of the participant to whom the PrEP control and the experimental PrEP was given, the dates they received drug and the amount dispensed. Any damaged or unused tablets that are returned will also be documented. The log will be checked during monitoring visits and at the end of the trial.

### 5.5.6 DOSE MODIFICATIONS & INTERRUPTIONS

PrEP must be interrupted if a participant suffers a serious adverse event that could be a drug reaction (see [section 7.1](#) and [Table 8](#) for definitions), or if their estimated glomerular filtration rate is confirmed to be <50ml/min using the Cockcroft-Gault formula with no alternative clinical explanation, pending further investigation or specialist referral.

The risk of renal toxicity from the drug needs to be weighed against the risk of acquiring HIV and study staff should seek advice from the TSG (see [section 14.2](#)) and have an informed discussion with the participant to enable them to decide whether PrEP can be reintroduced, potentially at a modified schedule of alternate days or 4 days a week.

TDF/FTC PrEP does not need to be interrupted during pregnancy, but the benefit of preventing HIV transmission in pregnancy needs to be weighed against the risk to the foetus and study staff should have an informed discussion with the participant to enable her to decide whether to continue PrEP.

There is insufficient information on TAF/FTC use in pregnancy and therefore this drug would need to be switched to TDF/FTC in the event of pregnancy.

## 5.6 UNBLINDING / UNMASKING

The vaccine component of PrEPVacc is placebo-controlled. The allocated treatment group will be blinded by the randomisation code. Neither the participant nor the investigator will know whether the participant has been allocated the active vaccine or the matched placebo, although staff administering the injection will be able to differentiate between 1ml and 0.45ml which would reveal those allocated to Group B or matched placebo. They will not know whether the product was active or placebo. Information on the allocation will be held centrally and locally as the vaccines and placebo are prepared locally by the pharmacist.

It may be necessary to unblind the allocation for a clinical reason during the working day or in an emergency. Participants will carry a contact card with the name and contact details for clinical staff at their centre, and an emergency number. Information on emergency unblinding can be found in the Safety Management Plan (SMP), held locally.

There may be a need to unblind the monitor for the purpose of ensuring the integrity of the randomisation. Unblinded data for this purpose should only be accessible to the monitor and provided by those who are preparing the reports by allocation for the Independent Data Monitoring Committee (see [section 9.4](#)). The blind shall be maintained for persons responsible for the ongoing conduct of the study.

Every effort will be made to inform participants which vaccine group they were allocated to at the end of the study.

The PrEP component is open-label and participants and investigators will know which of the two PrEP agents they have been allocated.

## 5.7 PROTOCOL TREATMENT DISCONTINUATION

In consenting to the trial, participants are consenting to receive vaccines, an offer of PrEP, to attend the visits for trial follow-up and to provide information that supports data collection.

Participants are not obliged to start PrEP or receive any vaccines.

An individual participant may stop injections early or be stopped early for any of the following reasons:

- ▶ Pregnancy in the participant
- ▶ HIV infection, confirmed by the local laboratory
- ▶ Unacceptable toxicity that precludes further injections
- ▶ Intercurrent illness that prevents further injections including emergent conditions that meet the exclusion criteria
- ▶ Withdrawal of consent for injections by the participant

A decision to discontinue further injections should be taken in consultation with the local PI and TSG.

An individual participant may stop PrEP early or be stopped early for any of the following reasons:

- ▶ HIV infection, confirmed by the local laboratory (see [section 6.7.1](#))
- ▶ Unacceptable toxicity that precludes further PrEP including an estimated glomerular filtration rate that is confirmed to be below 50ml/min using the Cockcroft-Gault formula
- ▶ Intercurrent illness that prevents further PrEP
- ▶ Withdrawal of consent for PrEP by the participant

As the participant's participation in the trial is entirely voluntary, they may choose to discontinue the trial treatment at any time without penalty or loss of benefits to which they are otherwise entitled.

Although the participant is not required to give a reason for discontinuing their trial treatment, a reasonable effort should be made to establish this reason while fully respecting the participant's rights.

Participants who have received at least one injection or one PrEP tablet will be asked to remain in follow-up. The participant may withdraw their consent to further visits at any stage of the trial. If a participant is withdrawn from follow-up, refer to [Section 6.10](#).

Data that are already collected from participants who stop follow-up early will be included in the analysis.

A decision to discontinue injections in participants may follow a recommendation by the IDMC and or TSC following the interim analysis (see [Section 9.4](#)) or following a temporary interruption (see [Section 5.2.7](#)) if the issue with a vaccine product cannot be resolved. Enrolled participants allocated to a discontinued regimen will not receive any further injections and will be informed verbally, and once approved in writing at the next visit. They will continue in follow-up according to the recommendation of the IDMC and TSC.

## **5.8 ACCOUNTABILITY & UNUSED VACCINES AND DRUG**

The Pharmacist will ensure that all products are dispensed in accordance with the protocol, the study specific SOM, and Local Pharmacy Working Instructions, and that records are maintained of receipt, dispensing and destruction of all supplies.

At the end of the trial, accountability will be checked by the designated member of staff responsible for the inventory and by the trial monitors. The Sponsor and the PI will retain copies of the complete accountability records and copies will be provided to the providers of the vaccines for the relevant product, and Gilead Sciences plc for the PrEP agents.

All used vials of injections and matched placebos will be kept at the respective site pharmacy for the duration required by the in-country regulatory authorities and will be destroyed in accordance with institutional rules and national regulations. Destruction of MVA vials will comply with the regulations on GMO products where these are considered GMO. The associated packaging will be retained at the pharmacy in compliance with the applicable national regulations and at least until monitoring is completed and monitors give instruction for their destruction.

For unused vaccine and PrEP products, the Sponsor will provide instructions for their return/destruction in agreement with the supplier of each product.

Following IMP destruction, the pharmacist at each site must complete a certificate of IMP destruction and send it to the MRC/UVRI and LSHTM with copies to the Sponsor, who will subsequently provide a copy to the respective product providers.

## **5.9 COMPLIANCE & ADHERENCE**

### **5.9.1 INJECTIONS**

All injections will be administered by site staff and recorded in the CRF according to the SOM. If an injection is not given within the ideal window (see [section 5.2.7](#)), this will be recorded in the CRF together with the reason. The data will be entered in the study database and compliance with the vaccine schedule will be reported to the TMG monthly by the MRC/UVRI and LSHTM coordinating team.

### **5.9.2 PREP**

Information about how to take PrEP will be provided to all participants.

Participants will be asked if they are taking PrEP, and if so how many days ago they last took PrEP, at screening and at visits 2, 4, 6-10, 12, 14, 15 and every 24 weeks thereafter. At visits 4, 6-10, 12, 14, 15 and every 24 weeks thereafter, participants will be asked if they have had sex without a condom and if so, the number of tablets they have taken in the two days before and after this sex act. This will be recorded in the CRF and study database.

Participants will be asked to provide a urine specimen at visits 4, 6, 7, 12, 15 and every 24 weeks thereafter according to Table 1. This will be tested in the clinic for the presence of tenofovir. Staff will explore the possible reasons for any discrepancies between the participant self-report and the result of the urine test with participants.

Blood will be collected at visits 2, 6, 9, 12 and 15 and every 24 weeks thereafter in order to prepare a dry blood spot (DBS) for later analysis of intracellular drug levels which can be categorised according to the number of tablets consumed per week as follows:

- ▶ 4 or more tablets a week
- ▶ 3 or less tablets a week
- ▶ no tablets

This information will be available for the analysis (see [section 9](#)) but not in clinic.

## 5.10 TREATMENT DATA COLLECTION

Study staff will collect information on the CRF and enter this in the study database, and Pharmacy staff will maintain the Injection and PrEP Accountability Logs which will be stored securely in the pharmacy according to the Local Pharmacy Working Instructions.

## 5.11 NON-TRIAL TREATMENT

### 5.11.1 MEDICATIONS NOT PERMITTED

The following treatments cannot be given concomitantly but would take priority over trial treatment if required to manage an emergent cancer or other serious condition:

- ▶ Chemotherapeutic drugs
- ▶ Immunomodulators and systemic immunosuppressive treatments
  - Glucocorticoids
  - Cyclosporine
  - Methotrexate
  - Interleukins and/or cytokines
  - Immunotherapies (including TNF blockers)

If it is necessary for a participant to receive treatment with any of these products, the PI or Medical Delegate should consult the TSG to discuss the planned treatment and plans for stopping the participant's vaccination schedule.

### 5.11.2 MEDICATIONS TO BE USED WITH CAUTION IN CONJUNCTION WITH PREP

Medications that can impair renal function should be used with caution in conjunction with either PrEP agent, particularly if the estimated glomerular filtration rate is <90 ml/min.

Co-administration of PrEP with drugs that are eliminated by active tubular secretion may increase concentrations of emtricitabine, tenofovir, or the co-administered drug.

### 5.11.3 OTHER VACCINATIONS

Vaccination with licensed vaccines should be avoided during the study because they may impact on the immune response. If needed for clinical reasons, PIs or Medical Delegate should consult the TSG

for advice with regard to timing, which will be up to 28 days later. Every effort will be made to vaccinate individuals after the key time points for collecting specimens for the immunological assays.

#### **5.11.4 TREATMENT AFTER HIV SEROCONVERSION**

Participants diagnosed HIV positive will be referred to local clinical centres for HIV treatment. Participants who are on PrEP when they have a confirmed HIV infection need a third drug to control viral replication. Treatment will be offered according to local and national guidelines, and organised through referral pathways according to local practice. If participants are taking PrEP at the time of diagnosis, the guidelines may allow them to continue the drug and add in a third agent.

#### **5.12 CO-ENROLMENT GUIDELINES**

Co-enrolment in previous or future trials is considered in [Section 3.4](#).

## 6 ASSESSMENTS & FOLLOW-UP

Potentially eligible participants will be identified largely from the Registration Cohort and informed about the trial at a routine visit or through contact with the study staff which might happen at a recruitment event. If interested, they will be provided with written information or provided with information using visual aids which may include a video. Regardless of whether or not they can read, they will be given the written information to take away and advised to go through this with a friend or family member. They will be encouraged to discuss participation with their partners, friends and family, and invited to make an appointment for a screening visit. Individuals who attend a recruitment event who are not enrolled in the Registration Cohort will be screened and may be enrolled in the cohort first.

The Delegation Log will determine which members of the study team are authorised to conduct the assessments and procedures described in this section. In order to ensure the study staff responsible for assessing adverse events remain blind to the vaccine allocation, pharmacists who are independent of the study team will be delegated with the responsibility of drawing up the vaccine or placebo.

Additional details can be found in the SOM, SMP and Laboratory Analytic Plan (LAP).

### 6.1 TRIAL ASSESSMENT SCHEDULE

The trial assessment schedule consists of a screening visit (visit 1), an enrolment visit which must take place within 8 weeks of the screening visit and which defines week 0 (visit 2).

The first injection will take place at week 0 (visit 2) and further injection visits are at visits 4, 8 and 12. The latest timepoint that the second, third and fourth injection visit can take place is indicated in Table 1 and is the end of the 13th, 40th and 68th week from enrolment respectively. Visits 3, 5, 6, 9, 10 and 13 have specific activities and procedures that relate to the collection of key safety and efficacy variables following the injection visits and the ideal timing relates to each injection. The earliest timepoint and upper target for visits is also given in Table 1. Provided visits occur in the period between the earliest timepoint and upper target there is no need to complete a protocol deviation form. If the participant has passed the upper target for the visit, a protocol deviation form should be completed.

Safety follow-up visits (or calls) to ask about all adverse events are at visits 3,5-7,9-11,13-15. After visit 15, follow-up visits will continue every 12 weeks for HIV testing through to the end of the trial, and participants will be asked about any serious illness or admission to hospital at these visits. These visits will continue to the last 3 months of the trial when everyone will have a final study visit. Additional visits may be undertaken if indicated, for example to investigate or follow-up an adverse event or abnormal laboratory result.

The clinic assessments, samples and volumes to be collected are outlined in **Table 1 Trial Assessment Schedule for Investigators**. Most of the visits during the trial require 10mls to be drawn for HIV tests and store. Larger volumes are required at visits when blood is collected for serology and PBMCs at visits 2 (133mls), 6 (43mls), 9 (138mls), 13 (129mls) and 15 (119mls). The maximum blood volume drawn for a participant who completes the schedule through to visit 15 is 679mL and will not exceed 200mL in any 3 month period, the equivalent of half a unit of blood. This does not include any additional blood volume that would be required if a safety or HIV test needs to be repeated. After visit 15, 10mL of blood will be collected every 12 weeks for HIV testing, and 5ml every 24 weeks for syphilis serology (if indicated). Amounts are specified in **Table 1**. The required volumes per visit together with sample collection and processing guidelines are described in detail in the LAP.

The visit windows are defined in the in [Table 1](#).

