|----------------------------------|-----------------------------------------------------------------------------------------------------------------------------------------------------------------------------------------------------------------------------------------------------------------------------------------------------------------------------------------------------------------------------------------------------------------------------------------------------------------------------------------------------------------------------------------------------------------------------------------------------------------------------------------------------------------------------------------------------------------------------------------------------------------------------------------------------------|
| Duration and blood volume | 
Participants continue from the screening visit (up to 8 weeks before enrolment) to the last visit, a minimum of 74 weeks (around 17 months) after enrolment.
 
679mls of blood will be collected from screening to 74 weeks of follow-up inclusive. Thereafter, 10mls will be collected every 12 weeks for HIV testing, with an additional 4mls for DBS and 5mls every 24 weeks for syphilis serology (if indicated), through to the final visit in the last 3 months of the trial.
 
If repeat safety or HIV tests are needed then up to 14ml and 10 mls respectively will be drawn.
 
If HIV status is confirmed as positive, 61ml of additional blood will be required at this visit for humoral and cellular responses virological analysis, including drug resistance testing.
 |

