## PREPVACC ASSESSMENT SCHEDULE

**Table 1:** Trial Assessment Schedule for Investigators (the target illustrates the ideal time for the gaps between immunisations)

| Visit number (V)                        | 1  | 2                | 3    | 4           | 5     | 6    | 7                | 8                | 9                | 10               | 11    | 12               | 13               | 14     | 15           | Follow-up after week 74 |             |       |
|-----------------------------------------|----|------------------|------|-------------|-------|------|------------------|------------------|------------------|------------------|-------|------------------|------------------|--------|--------------|-------------------------|-------------|-------|
| Target (wks or Visit +wks)              | -8 | 0                | 1    | 4           | V4+1  | V4+4 | V4+12            | V4+20            | V8+2             | V8+6             | V8+14 | V8+24            | V12+2            | V12+14 | V12+26       | Every 12wks             | Every 24wks | Final |
| Upper Target                            |    |                  | 2    | 7           | V4+2  | V4+5 | V4+16            | V4+22            | V8+4             | V8+7             | V8+18 | V8+26            | V12+4            | V12+18 | V12+32       | +6                      | +6          |       |
| Earliest timepoint                      |    |                  | 1-4d | 3           | V4+3d | V4+3 | V4+11            | V4+17            | V8+1             | V8+5             | V8+13 | V8+19            | V12+1            | V12+10 | V12+22       | -6                      | -6          |       |
| Latest timepoint for immunisation/visit |    | 0                |      | End of wk13 |       | V8-1 |                  | End of wk40      | V12-1            |                  |       | End of wk68      |                  |        | End of trial |                         |             |       |
| Immunisation                            |    | x                |      | x           |       |      |                  | x                |                  |                  |       | x                |                  |        |              |                         |             |       |

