| TFV DP levels in RBCs       |    |                  |      |             |       |      |                  |                  | x                |                  |       | x                |                  |        | x            |                         | x           |       |
| Risk and/or adherence                   | x  |                  |      | x           |       |      | x                | x                | x                | x                |       | x                |                  | x      | x            |                         | x           |       |
| STI screen                  | x  |                  |      |             |       |      |                  |                  | x                |                  |       | (x)              |                  |        | (x)          |                         | (x)         |       |
| HIV and store                           | x  | x                |      | x           |       | x    | x                | x                | x                | x                | x     | x                | x                | x      | x            | x                       | x           | x     |
| Immunology and store        |    | x                |      |             |       | x    |                  |                  | x                |                  |       |                  | x                |        | x            |                         |             |       |
| Store for HLA                           |    | x                |      |             |       |      |                  |                  |                  |                  |       |                  |                  |        |              |                         |             |       |
| Total blood volume(ml)      | 29 | 133              | 0    | 24          | 0     | 43   | 10               | 10               | 138              | 10               | 10    | 14               | 129              | 10     | 119          | 10                      | 14          | 10    |

SAE= Serious Adverse Events: information will be collected throughout

 (x) additional routine safety or pregnancy tests may be needed to follow-up a side effect or previously abnormal value. Routine safety labs recorded are Hb, creatinine, AST/ALT, alkaline phosphatase, total Bilirubin and glucose.

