## 6.3 PROCEDURES AT ENROLMENT

This visit should take place within 8 weeks following the screening visit. If more than 8 weeks have elapsed study staff should consult the SOM to find out which screening assessments need to be repeated.

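### Section 6.1 limits blood draws to 200 mL in any 3 months, but Table 1 gives 229 mL when screening falls within about 5 weeks of enrolment at target visit times

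*Protocol*

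**What the plan says.** Section 6.1 gives a total and a ceiling in one sentence. The total is stated as "The maximum blood volume drawn for a participant who completes the schedule through to visit 15 is 679mL", and the same sentence continues that the volume "will not exceed 200mL in any 3 month period". The sentence after it excludes only the extra blood needed to repeat a safety or HIV test; footnote 5 to Table 1 makes the same exclusion.

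The Summary of Trial fixes the period that the total covers: "679mls of blood will be collected from screening to 74 weeks of follow-up inclusive".

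The volume row of Table 1 begins "Total blood volume(ml) 5 | 29 | 133 | 0 | 24 | 0 | 43", which are the figures for visits 1 to 6. Section 6.1 repeats the larger draws: "at visits 2 (133mls), 6 (43mls), 9 (138mls), 13 (129mls) and 15 (119mls".

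The target row of Table 1 begins "Target (wks or Visit +wks) | -8 | 0 | 1 | 4 | V4+1 | V4+4". Visit 2 is therefore week 0, visit 4 is week 4, and visit 6 is week 8.

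Section 6.3 says of enrolment: "This visit should take place within 8 weeks following the screening visit". Section 6.1 and the Summary also treat 8 weeks as an outer limit. No minimum gap between screening and enrolment is given.

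**The concern.** The ceiling is written without conditions and for any 3-month period. Visits 2 to 6 alone use all of it, and the screening draw comes before them at an interval that the protocol leaves open between 0 and 8 weeks. A participant seen at target visit times, with no deviation and no repeat test, can therefore exceed a limit that the protocol states as fact.

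No efficacy analysis depends on this. What is at stake is whether a participant-protection statement, in a document submitted to ethics committees, is true of the conduct it permits. A site that follows Table 1 cannot be sure of keeping to it.

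**Working it through.** **Inputs.** Volumes and visit times come from Table 1; the ceiling, the total and the exclusion from section 6.1; the screening interval from sections 6.1 and 6.3. The protocol does not say how many weeks make 3 months. I assume 13 and show 12 as a check.

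**Step 1: reproduce the stated total.** Visits 1 to 15:

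29 + 133 + 0 + 24 + 0 + 43 + 10 + 10 + 138 + 10 + 10 + 14 + 129 + 10 + 119 = 679 mL.

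This matches. Without screening it is 679 − 29 = 650 mL, so the stated total includes the screening draw.

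**Step 2: the ceiling counted from enrolment.** Visits 2, 4 and 6 (visits 3 and 5 take no blood):

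133 + 24 + 43 = 200 mL, complete at target week 8. The ceiling is met with nothing to spare.

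**Step 3: add screening.**

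29 + 133 + 24 + 43 = 229 mL. Excess = 229 − 200 = 29 mL, and 29/200 = 14.5%.

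**Step 4: when the four draws share one window.** The largest screening gap that still fits is the window length minus the week of visit 6.

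| Visit timing | Visit 4 | Visit 6 | Gap limit, 13 weeks | Gap limit, 12 weeks |
|---|---|---|---|---|
| Earliest | week 3 | 3 + 3 = week 6 | 13 − 6 = 7 weeks | 12 − 6 = 6 weeks |
| Target | week 4 | 4 + 4 = week 8 | 13 − 8 = 5 weeks | 12 − 8 = 4 weeks |
| Upper target | week 7 | 7 + 5 = week 12 | 13 − 12 = 1 week | 12 − 12 = 0 weeks |

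Section 6.1 says that visits between the earliest timepoint and the upper target need no deviation form, so all three rows are permitted conduct.

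**Step 5: the rest of the schedule.** At target timing the largest 13-week sum after this stretch is 158 mL, for example visits 7, 8 and 9: 10 + 10 + 138. On the target schedule the problem is therefore confined to screening through visit 6.

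**The case against.** The best defence is that the ceiling was probably counted from enrolment, where the sum is exactly 200 mL. The target row also puts screening at week −8, which is 16 weeks before visit 6. A participant seen at every target in that row meets the ceiling. Both observations are fair, but they do not rescue the wording. It covers any 3-month period, it excludes only repeat tests, and it shares a sentence with a total that includes screening. Elsewhere the 8 weeks is an outer limit, not a fixed interval.

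The objection does rule out several stronger readings that a reader might infer:

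- **That everyone screened within 5 weeks exceeds the ceiling.** The 5-week limit belongs to target timing and a 13-week window. At the upper targets it falls to about 1 week. If visit 4 is near its latest timepoint, the end of week 13, visits 2 to 6 no longer fit in 3 months.
- **That many participants are affected.** The protocol gives no distribution of screening gaps. Section 4 requires laboratory results before randomisation, so very short gaps may be uncommon.
- **That the figure is 253 mL.** This adds one repeat of each test (14 + 10 mL), which section 6.1 expressly leaves out. The comparable figure is 229 mL.
- **That the participant information is wrong.** It is a separate document and is not available here.
- **That haemoglobin or safety is harmed.** Nothing in the protocol shows an effect of an extra 29 mL.
- **That 229 mL is the true maximum and should replace 200 mL.** The latest-timepoint row of Table 1 lets visit 9 run to one week before visit 12, although a deviation form is then needed. Visits 9, 12 and 13 would give 138 + 14 + 129 = 281 mL in about 3 weeks.

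**Conclusion.** The statement is wrong as written. The protocol's own volumes give 229 mL against a stated maximum of 200 mL, before any repeat test. At target timing the ceiling holds only if screening is more than about 5 weeks before enrolment (about 4 with a 12-week window), or if the screening draw is not counted.

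The conclusion rests on Table 1 as printed, on the screening draw counting towards the ceiling (as it does towards the 679 mL), and on 3 months meaning 12 to 13 weeks. The threshold shifts with visit timing; the 229 mL does not. How often the ceiling would be exceeded cannot be judged from the protocol. The point is a contained inconsistency in a participant-protection figure, with no bearing on power or the efficacy analyses.

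**What to change.** Reconcile the 3-month statement in section 6.1 with the volumes and visit windows in Table 1 and with the screening interval in sections 6.1 and 6.3, so that the stated maximum is true for all conduct the protocol permits. Whether the ceiling, the volumes or the timing changes is for the sponsor to decide. The revised text should say whether the screening draw counts and how long 3 months is. It should be checked against the earliest, upper-target and latest-timepoint rows, not only the target row. The sponsor should also check whether any participant information repeats the 200 mL figure.

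If only the statement changes, the cost is a short wording correction in the protocol, and in any participant document found to carry the figure. Changing volumes or visit timing would also mean revising Table 1 and the related procedures.
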